| [name] | Assistant Lecturer,  Department of Mental Health  Kamuzu University of Health Sciences (KUHES) | **MBBS**, University of Malawi, College of Medicine  **MMed** in Psychiatry, KUHES | General Adult Psychiatry,  Child and adolescent mental health services,  Psychogeriatrics,  Addictions,  Psychotherapy,  Liaison psychiatry and therapeutics |

1. **Background**

Healthcare provision can be stressful even in normal times and maintaining the mental wellbeing of health workers is of utmost importance for optimal and safe patient care (Søvold et al., 2021). The COVID-19 pandemic of 2020/21 has overwhelmed countries’ health systems and increased care-related pressure manyfold in the effort of ensuring patient care and staff safety. Added stress of too many life and death decisions, physical exhaustion, lack of protective equipment, and fear of infecting themselves or their families threatens health workers’ mental wellbeing daily. Over the last two years, an increasing number of studies report a high proportion of health professionals globally suffering from depression, anxiety, and burnout. A systematic review of 59 studies by Muller et al. (2020) found that a median of 24% of health workers suffered from anxiety, 21% from depression, and 37% from distress. Nochaiwong et al. (2021) reported slightly higher levels in a meta-analysis from 36 countries – 8.0%for depression; 26.9% for anxiety; 24.1% for post-traumatic stress symptoms; 36.5% for stress; and 50.0% for psychological distress. Recent studies from Sub-Saharan Africa showed similar levels. In a multi-centre cross-sectional study from Ghana, Ofori et al. (2021) found that 21.1%, 27.8% and 8.2% had depression, anxiety and stress, respectively. Research not yet peer reviewed from Ethiopia found a prevalence of depression, anxiety and psychological distress was 20.2%, 21.9% and 15.5% respectively. Data from South Africa suggest much high levels of metal disorders of around 50% among all types of health workers due to work-related stress (Msomi, 2021). While there are no peer-reviewed studies yet from Malawi, initial research using a small sample of nurses and the Coronavirus Anxiety Scale suggests that 26% (n=26) of respondents had COVID-19 related anxiety and 48% (n=49) functional impairment (Chorwe-Sungani, 2021).

Mental disorders not only pose threats to patient safety and health workers’ quality of life, but they also come at high economic costs. A World Health Organization (WHO)-led study well before the COVID-19 pandemic found that depression and anxiety disorders cost the global economy US$1 trillion each year. A return on investments between 2.3 and 5.7 to 1 was estimated for scaled up treatment of these mental disorders (Chisholm, et al. 2016). Mental health interventions include basic psychosocial counselling for mild cases, and either basic or more intensive psychosocial treatment plus antidepressant drugs. Over the last decade computer- or internet-based cognitive behavioural therapy (c-CBT or i-CBT) has been tested and implemented as an alternative to in-person treatment of mental health issues. Research has shown that computerized CBT-based self-administered interventions improve depression and anxiety in adults. A meta-analysis by Grist and Cavanagh (2013) of 49 RCTs revealed a significant medium effect size (g=0.77, 95% CI 0.59-0.95) for computerized CBT (CCBT) for depression and anxiety.

Another meta-analysis by Andrews et al. (2010) of 22 RCTs found an even greater effect size (g=0.88, 95% CI 0.76-0.99). However, in a recent systematic review Christ et al. (2020) found small to medium posttreatment pooled effect sizes regarding depressive symptoms (g=0.51, 95% CI 0.30-0.72) and anxiety symptoms (g=0.44, 95% CI 0.23-0.65) of c-CBT for reducing anxiety and depressive symptoms in adolescents and young adults compared with passive controls. Clinical trials have established that a mobile application can effectively deliver a CBT program for the treatment of depression (Watts et al., 2013), self-management of chronic pain conditions (Kristjánsdóttir et al., 2013) and social anxiety disorder (Dagöö et al., 2014). C-CBT or i-CBT can lower the barrier to seek help and it is especially important where access to psychologists and therapists is low, which is the case in most countries in Sub-Saharan Africa (Bakker et al., 2016).

C-CBT or i-CBT have evolved into interactive chatbots that are driven by artificial intelligence. Chatbots are conversational agents and include the recent entrant Vitalk. Vitalk distinguishes itself that it is available for the public as well as a version adapted for health professionals. The effectiveness of the public version has been established through a panel study without control group by Daley, Hungerbuehler et al. (2020) in Brazil, who found a large post-intervention effect size of Cohen’s d of -0.81 or greater for anxiety, depression and stress. The version for health workers has been pilot tested in Malawi, a country where access to mental health therapy is very limited. Statistics on the mental health force in Malawi show that the country has only 0.02 psychologists, 0.01 psychiatrists and 0.04 occupational therapists per 100,000 populations (WHO, 2018). Only recently has the country successfully trained three psychiatrists. This situation is worsened by the frequent deployment of mental health professionals especially psychiatric nurses to other duties such as maternity services (Kauye, 2008).

To date, there have been few studies for establishing the effectiveness of chatbots and even fewer RCTs. Most of these trials were based on small samples of 70 participants or less, had a short duration of 2-4 weeks, suffered from serious biases, and fell short of establishing that chatbots lead to improved mental health outcomes. All trials were conducted in high-income countries, none in low resource settings (Abd-Alrazaq et al., 2020). No RCTs have been conducted to assess the effectiveness of chatbots in improving the mental health status of health workers specifically (Bakker et al., 2016).

The proposed RCT addresses this evidence gap about the use and effectiveness of chatbots within the health workforce. Building on the earlier pilot test, a RCT will be conducted in Malawi to explore whether a chatbot, Vitalk, is an acceptable source of advice and counselling for health workers to effectively cope with work-related depression, anxiety and burnout and how resilience-building behaviours can mitigate poor mental health outcomes.

1. **Research Objectives**

**Main research objective**

The main objective of this study is to test the *null hypothesis that the use of a chatbot such as Vitalk over a period of eight weeks does not result in different mental health outcomes in a treatment and control group* of health workers in Malawi. The null hypothesis will be tested in a two-arm RCT comparing the pre-treatment to post treatment scores using standardized scales for depression, anxiety, resilience, and burnout.

**Specific research objectives**

In addition to testing the null hypothesis, this study intends to achieve the following specific objectives:

1. To evaluate whether the levels of engagement and continuity of use of Vitalk are adequate to meet the need for mental health support (rate of adoption and continuity).

2. To explore whether the frequency and duration of interaction with Vitalk are significant predictors of mental health outcomes (stickiness/intensity of use).

3. To establish whether the use of Vitalk significantly reduces the number and duration of sub-clinical and clinical episodes of depression, anxiety, resilience, and burnout over the study period (effectiveness).

4. To discover which features of Vitalk are liked or disliked; what improvements are suggested by users; and whether user experience drive stickiness (user experience).

**Specific research questions**

The specific research questions of this study are as follows:

1. Are the levels of engagement and continuity of use of Vitalk adequate to meet the need for mental health support (rate of adoption and continuity)?

2. Are the frequency and duration of interaction with Vitalk statistically significant predictors of mental health outcomes (stickiness/intensity of use)?

3. Does the use of Vitalk significantly reduce the number and duration of sub-clinical and clinical episodes of depression, anxiety, resilience, and burnout over the study period (effectiveness)?

4. Which features of Vitalk are liked or disliked; what improvements are suggested by users; and does user experience drive stickiness (user experience)?

1. **Research Methodology**

4.1. Study Design, Randomization, And Blinding

This study is guided by the conceptual framework shown in Figure 1 below. The study is a two-arm, parallel randomized controlled trial with a pre-treatment assessment, 8-week intervention period and mid-study assessments at 4-5 weeks and an end-of-study assessment at 9 weeks^^[[1]](#footnote-1)^^. Interested study participants will be randomly assigned to either the treatment or control group at the time of registration. Vitalk, the developer of the app, will create a study web portal where study participants register, give their consent, are assigned to one of the study arms, are given a unique study identification number, and enter their demographic information. Depending on the random assignment, participants will be taken to either the treatment app, Vitalk, or the website for the control group. This is a single blinded design because only the research team will be blinded to the study arm assignments; all participants in both study arms will be told they are participating in ‘*an online self-help for mental wellbeing*’.

[figure not shown]

*Figure 1. Study framework*

Participants will be required to seek approval from their employers to participate in the study, because some activities will occur during working hours, but no information collected during the trial that could identify participants or their facilities of affiliation will be shared with the employers. A trial manager, someone appointed by Vitalk and the Department of Psychology (UNIMA) who is not part of the research team, will provide technical support in case participants encounter difficulties with the study portal or the Vitalk app and be therefore privy to the group assignment, but this information will not be shared with the research team during the study. The study portal and control group website will be optimized for and accessible through smartphones. Vitalk is a smartphone app for Android and iOS.

- 1. Treatment and control group interventions
[figure not shown]

     1. Vitalk chatbot app (treatment group, *active*)

Originating from Brazil, Vitalk is an automated chatbot delivering mental health content to its users using a conversational format, with the aim of improving well-being by reducing stress, anxiety and depression using a preventative approach to mental health (Daley, Hungerbuehler et al., 2020). The Vitalk app uses psychoeducation, cognitive restructuring, behavioral activation, gratitude, and practical exercises (such as breathing, relaxation and meditation) to bring about improvements in users’ mental health (ibid). These techniques and strategies are rooted in CBT and Positive Psychology, two commonly used psychotherapy methodologies that have been used widely in various settings and have registered high effectiveness among patients presenting with various psychological challenges (Beck, 2011; Seligman, 1998; Wills, 2009). Only the treatment arm of the study will have access to Vitalk.

- - 1. Mental health resource website (control group, *passive*)

The control arm of the study will have access to a website with links to mental health resources from WHO and other self-help providers as well as contact information for psychologists and mental health counselors in Malawi. This website consists of a few pages with basic mental health and coping information, links to mental wellbeing resources, mood meter and standardized mental health tests. Its content is static without user interaction beyond clicks to access web-based
[figure not shown]
mental health resources. Whether or not these resources are used depends entirely on the initiative of control group participants.

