Lastly, a clinical exclusion criteria will apply to all health workers currently under treatment for a severe mental disorder and to all study applicants with severe symptoms of depression, anxiety or burnout according to their initial scores from standard mental health tests. These conditions will include suicidal ideation. Those excluded will not have their identity revealed, but they will simply not be able to stay registered for the study. Participant meeting the exclusion criteria will be offered resources for self-help and contacts of mental health counselors.

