**Study period**

[figure not shown]
*Figure 2. Study process and timeline*

This trial is scheduled to span 56 calendar days, from the week beginning on the 4^th^ of October 2021 until the 26^th^ of November 2021. The entire process and timeline are shown in Figure 2. Study participants in both the treatment and control groups will begin their participation in this project by attending a half-day workshop prior to the start of the trial before October 4, which shall serve a dual purpose. Firstly, during this workshop participants shall receive a presentation about general tenets of mental health, how mental health affects work performance, the impact of one’s mental health upon their work, and a description of the four specific areas of mental health that will be assessed: namely anxiety, depression, resilience, and burnout. Secondly, participants will be provided with an overview over the study of ‘*an online self-help for mental wellbeing*’ and the eligibility criteria, but NO specifics about interventions in the treatment or control groups will be mentioned. Only information pertaining to both groups will be discussed.

At the workshop, participants will have the option to join the trial or to leave. Those opting to join will be directed to the study web-portal, provide their consent, complete a pre-screening to establish eligibility, and register for the trial. All participants eligible at this stage shall then complete the initial mental health assessment to assess the initial scores for depression, anxiety, resilience, and burnout. Anybody scoring at the severe level for any of the four scales or showing signs of suicidal ideation will be excluded from the trial and be provided with contacts to mental health professionals in Malawi and Vitalk-affiliated psychologists. All participants passing these final eligibility criteria shall be admitted to the trial and familiarized with links to mental wellbeing resources on the internet and contacts with local psychologists and mental health counselors.

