Resilience refers to the ability to withstand or adaptively recover from stressors. Resilience also promotes psychological and physical well-being. Resilience is negatively correlated with symptoms of generalized anxiety and posttraumatic stress and positively correlated with gratitude, optimism, and positive affect. The five characteristics of resilience are meaning and purposeful life, perseverance, equanimity, self-reliance, and existential aloneness (Wagnild, 2009a). Total scores are categorized as very low (14–56), low (57–64), on the low end (65–73), moderate (74–81), moderately high (82–90), and high (91–98). RS-14 has been validated and used in low and middle-income countries (Wagnild, 2009b; Siriwardhana, 2015)

*Oldenburg Burnout Inventory (OLBI)*

Burnout is linked to relatively high work requirements and limited resource availability for managing them, which leads to negative emotional states. Therefore, the discrepancy between resources and challenges creates a significant negative emotional state. The OLBI has 16 items, eight to describe exhaustion and eight to describe disengagement (Demerouti & Bakker, 2008). The questionnaire includes both straight and reversely worded items in both dimensions. Low, medium or high OLBI-D scores are based on scores above or below 1 standard deviation of the mean (mean= 2.15, SD = 0.52; ≤1.62= low, 1.63 to 2.67= medium, ≥2.68= high). OLBI has been validated and used in low and middle-income countries (Kaggwa et al., 2021).

Stress is not included in these assessments, because past evaluations have shown almost universally high stress levels pre- and post-intervention, which makes it impossible to use it as an outcome if there are no discriminating factors.

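### Participants are allocated at registration, before the baseline tests that settle eligibility, so an unstated share is excluded after allocation; the severity rule applied there is also inconsistent

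*Combined protocol and SAP*

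**What the plan says.** **Timing of allocation.** Section 4.1: "Interested study participants will be randomly assigned to either the treatment or control group at the time of registration". It lists the portal steps as: "register, give their consent, are assigned to one of the study arms, are given a unique study identification number, and enter their demographic information". It adds: "Depending on the random assignment, participants will be taken to either the treatment app, Vitalk, or the website for the control group".

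**Timing of eligibility.** The Study period section says that those who join at the workshop "provide their consent, complete a pre-screening to establish eligibility, and register for the trial". It continues: "All participants eligible at this stage shall then complete the initial mental health assessment to assess the initial scores for depression, anxiety, resilience, and burnout". Then: "Anybody scoring at the severe level for any of the four scales or showing signs of suicidal ideation will be excluded from the trial". Only those who pass are admitted. The same section says that admission is not announced at the workshop. A later email either gives the link for the person's arm or tells the person that they are not eligible.

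**The severity rule.** The clinical exclusion under Study participants covers applicants "with severe symptoms of depression, anxiety or burnout according to their initial scores from standard mental health tests", which is three constructs. The Study period wording covers four. Under Data collection instruments, GAD-7 and PHQ-9 each have a category called severe. RS-14 runs from very low to high. For burnout: "Low, medium or high OLBI-D scores are based on scores above or below 1 standard deviation of the mean".

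**Numbers and analysis.** The Sampling method section goes from 128 to 512 to 640 per arm, 1,280 in total. The last step allows 20% for ineligibility and other losses together. The Data analysis method section defines no analysis population and does not say what happens to people who are allocated and then found ineligible.

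**The concern.** Eligibility should be settled before allocation, so that the randomised groups are also the analysed groups. Here the last eligibility gate comes after allocation, and it uses baseline scores on the outcome scales themselves. Two consequences are possible, and they differ in weight.

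- If nobody's route through the portal depends on arm until eligibility is settled, exclusions fall on both arms alike. The trial then loses numbers, some chance balance between arms, and a clear all-randomised set to report.
- If the arm affects where or how the baseline tests are taken, the proportion who complete them and the proportion excluded could differ by arm. Randomisation would then no longer protect the comparison.

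A severity rule that cannot be applied as written makes either case worse, because someone must decide its meaning after arms have been assigned.

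**Working it through.** **1. Order of steps, side by side**

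| Step | Section 4.1 | Study period |
|---|---|---|
| Consent | after registering | before registering |
| Pre-screen (questionnaire in Annex 1.2.1) | not mentioned | before registering |
| Registration | first | after consent and pre-screen |
| Arm assigned | at registration | not stated |
| Four baseline tests | not mentioned | after registration |
| Exclusion on scores | not mentioned | after the tests |
| Arm link given | no time stated | email after the workshop |

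Combining the two gives: consent, pre-screen, registration with allocation, baseline tests, exclusion, email. The pre-screen (cadre, English, smartphone, current treatment, suicidal thoughts) precedes allocation. The score-based exclusion follows it.

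**2. The plan's own sample-size chain**

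Inputs from Sampling method: difference 1.5, SD of the difference 6, power 80%, significance 5% (two-sided assumed), losses of 75% and 20%.

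- Normal approximation: (6 × (1.960 + 0.842) / 1.5)² ≈ 125.6, so 126. The paired t calculation gives 128 (power 0.8015), as stated.
- 128 / (1 − 0.75) = 512.
- 512 / (1 − 0.20) = 640, and 2 × 640 = 1,280.

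The chain reproduces.

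**3. How many could leave after allocation**

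The 20% is 640 × 0.20 = 128 per arm. It is conditional, pools ineligibility with other losses, and has no timing. Let s be the fraction lost before registration (assumed; the documents give none). Then 640 − 128s are allocated per arm and 128(1 − s) leave afterwards.

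| s | Allocated per arm | Leave after allocation | Share |
|---|---|---|---|
| 0 | 640 | 128 | 20.0% |
| 0.25 | 608 | 96 | 15.8% |
| 0.50 | 576 | 64 | 11.1% |
| 0.75 | 544 | 32 | 5.9% |
| 1 | 512 | 0 | 0% |

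The third column still includes losses for other reasons, so exclusions on severity alone would be fewer.

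The 20% is a planning figure, not a ceiling. If 25% or 30% of 640 were lost after allocation, 480 or 448 would remain. At the planned 75% dropout that leaves 480 × 0.25 = 120 or 448 × 0.25 = 112 evaluable per arm, against 128.

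**4. Sensitivity to the undefined burnout threshold**

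The plan's high OLBI band starts at 2.68, with mean 2.15 and SD 0.52. Suppose, purely for illustration, that high were read as severe and that scores were normal with those values. The excluded share would be P(Z ≥ (2.68 − 2.15)/0.52) = P(Z ≥ 1.02) ≈ 15.4%, or about 99 of 640, on burnout alone. The band starts about one SD above the mean, so a figure near this size follows by construction. It shows that the reading matters; it does not forecast this trial.

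**5. Where the baseline tests are taken**

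The Study period section sends everyone to the study portal. Annex 1.2.3 lists all four scale scores among the data collected by the control website or by Vitalk, and the description of the control website includes standardised tests. The documents do not say which platform delivers the baseline tests.

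**The case against.** The strongest reply is that the arm stays hidden until eligibility is settled. Everyone uses one portal at a workshop, exclusion is by score, the research team is blinded, and a single later email carries both the admission decision and the arm link. Excluding people by the same rule in both arms, on scores given before they know their arm, costs numbers and chance balance but creates no systematic bias. That stands, provided the email procedure is followed.

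The contrary evidence is also limited. Section 4.1 does not say when participants are taken to their arm's platform. Annex 1.2.3 lists completed registrations as well, and those happen on the study portal, so it cannot show where the baseline tests are taken. The risk is left open rather than demonstrated.

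The order itself could be questioned. Section 4.1 lists registering before consent and the Study period section reverses this, so the section 4.1 list is not a dependable chronology. The timeline figure is not available in the text reviewed. However, the statement that assignment happens at registration does not depend on that list, and the tests clearly follow registration.

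A reader might infer three stronger things that the documents do not support:

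- *That a fifth of each arm will be excluded after allocation.* The 20% is conditional, includes other losses, and covers pre-screen failures that occur before registration.
- *That exclusions will differ by arm.* No passage establishes this.
- *That the resulting bias can be stated in scale points.* This needs an exclusion rate for each arm and a baseline SD. The plan gives neither; its SD of 6 is for the pre-post difference.

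Finally, the severity wording is a separate defect that would exist whenever allocation took place. That is fair, but it operates at the same step and belongs in the same correction.

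**Conclusion.** The point holds in a limited form. As written, allocation follows pre-screening but precedes the tests that decide final eligibility, so an unstated share is excluded after allocation by design. The only guide to size is the pooled 20% allowance. The maximum under that allowance, 128 per arm, requires the whole of it to fall after allocation; 32 to 96 per arm follows from assumed splits.

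If the arm is disclosed only by the later email, the harm is to numbers, chance balance and the definition of the all-randomised set. Arm-dependent completion or exclusion becomes possible only if participants reach their arm's platform at registration or take the baseline tests there. The documents leave both open.

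The inconsistency in the severity rule is certain: three scales against four, and no severe category for two of the four. Those passages must be reconciled. This review takes no position on which scales or bands should exclude.

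Both matters need settling before the portal opens, because the order cannot be changed for anyone already allocated.

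**What to change.** 1. **Reorder the portal:** consent; pre-screen; registration and demographics; all four baseline tests on the common portal; final eligibility check; randomisation of those who pass; then the email with the arm link. Align section 4.1 and the Study period section with this order.
2. **State the numbers.** On the plan's own figures about 1,280 are recruited and 1,280 × 0.80 = 1,024 are randomised, 512 per arm. This treats the whole 20% as lost before randomisation; if some of the other losses come later, the number randomised is higher.
3. **Define the analysis set** in the Data analysis method section as all randomised participants.
4. **Reconcile the severity wording** in Study participants, Study period and Data collection instruments. State which scales exclude and at which band, and fix this in the portal before it opens.

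The cost is a change in the order of portal screens and a few sentences of protocol. No extra participants are needed, and no delay should follow, because the arm link is already sent by email after the workshop.
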